### Randomization, allocation concealment, and blinding

2.5

The randomization sequence assigning participants to the study groups (i.e., exercise intervention group and usual care wait-list control group) will be generated by a computerized algorithm with no human access and implemented via the centralized Diactive-1 web-based platform. The algorithm will use a non-stratified randomization scheme with small, randomly varying even block sizes (i.e., 2, 4, 6, and 8 participants). Each block will contain an equal allocation ratio between the two groups (50%–50%), with the order of assignments within each block randomly permuted, thereby ensuring balance between groups throughout recruitment while minimizing predictability of the sequence. Because recruitment per hospital may vary, randomization will be centralized and non-stratified, with hospital-level clustering accounted for in the mixed-effects models. To ensure allocation concealment, randomization will be automatically performed after completion of the baseline clinical visit and entry of the corresponding clinical data, before the 7-day diabetes-related data-collection period.

Participants and healthcare professionals cannot be blinded due to the nature of the intervention. Outcome processing and statistical analyses will be performed using coded group allocation whenever feasible. The statistical analyst will remain blinded to group identity until the primary analyses have been completed. All hospitals and participants registered on the Diactive-1 web-based platform will be coded using alphanumeric identifiers.

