### Sample size and recruitment

2.4

Based on preliminary 12-week intervention data from the previous Diactive-1 trial, the between-group difference in handgrip strength z-score was 0.24 units, corresponding to an approximate standardized effect size of Cohen’s d = 0.56 (10). Using G*Power for an independent-samples comparison with a two-sided α = 0.05, 134 evaluable participants (67 per group) would provide 89.6% power, rounded to approximately 90% (27). After allowing for an anticipated attrition rate of 15%, the recruitment target was set at 158 children and adolescents in total, with 79 participants allocated to the intervention group and 79 to the usual-care group (28). Sampling will be extended until the end of the recruitment period, incorporating as many participants as possible.

Because participants will be individually randomized within hospitals, this is not a cluster-randomized trial. Nevertheless, hospital-level effects will be accounted for in the planned mixed-effects analyses by including hospital as a random effect. As the actual hospital-level ICC is not yet known, a conservative *a priori* sensitivity analysis was conducted using the design effect DE = 1+(m−1)×ICC. Assuming a mean hospital size of approximately 14.5 participants and 15% attrition, ICC values of 0.01, 0.02, and 0.05 corresponded to effective sample sizes of approximately 120, 107, and 81 participants, with estimated powers of approximately 86%, 82%, and 70%, respectively. Thus, the planned recruitment is expected to retain more than 80% power under hospital-level ICC values of up to 0.02, whereas greater clustering would result in reduced power. Recruitment may continue beyond the target sample until the end of the prespecified recruitment period.

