#### Anthropometric parameters and stage of maturity

2.10.5

Standing height will be measured to the nearest 0.1 cm using a SECA 213 stadiometer, with participants barefoot, heels together against the base of the vertical column, back straight, and head positioned in the Frankfurt horizontal plane (41). Body weight will be measured to the nearest 0.1 kg using a SECA 869 electronic scale, with participants barefoot and wearing light clothing. BMI will be calculated as weight in kilograms divided by height in meters squared (kg/m^2^).

Peak height velocity (PHV) will be estimated using the Moore equation (42), and categorized as prepubertal (≤−1 year from PHV), peri-pubertal (−1 to 1 year from PHV), or post-pubertal (≥1 year from PHV) (43). Pubertal status will be assessed using Tanner criteria (44), which will be examiner-rated (i.e., physician-assessed) during the clinical visit.

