Effect of the intervention: The intervention effect will be estimated for the primary outcome using linear mixed-effects models under the ITT principle, with participants analyzed according to randomized allocation. Baseline and 12-week outcome values will be jointly modeled as repeated outcome measurements using data in long format. Models will include fixed effects for group, time, and the group × time interaction, with random intercepts for hospital and participant nested within hospital. Because baseline outcome values are included as repeated measurements, they will not be entered as separate covariates. The primary treatment effect will be estimated from the group × time interaction, representing the between-group difference in change from baseline to 12 weeks (i.e., over time). The same modeling framework will be applied to the prespecified secondary continuous outcomes, with correction for multiple testing within outcome families using the Benjamini–Hochberg false discovery rate procedure (66).

The primary model for handgrip strength will include no additional covariates. Prespecified adjusted models for glycemic outcomes will additionally include baseline daily insulin dose and baseline carbohydrate intake, whereas models for daily insulin dose will include baseline carbohydrate intake. These covariates were selected *a priori* because of their established prognostic relationships with the corresponding outcomes. No other covariates will be included in these prespecified models (67). Any additional unplanned adjusted analyses will be clearly identified as *post hoc* sensitivity analyses and will not be selected solely on the basis of observed baseline differences between groups (62).

In addition to the primary ITT analysis, per-protocol (PP) analyses will be conducted including intervention participants who complete an average of at least two resistance-training sessions per week during the 12-week intervention (68), provided that these sessions are reasonably distributed across the intervention period rather than concentrated in a limited number of weeks, and usual-care participants with available primary outcome data and no major protocol deviations.

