Unstandardized coefficients with 95% confidence intervals (CIs) will be used to estimate marginal means and group contrasts over time, which will be reported as mean differences (MDs). Standardized effect sizes, including Cohen’s d when appropriate, will be reported as complementary measures (69). For categorical outcomes, between-group effects will be estimated using risk differences (RDs) and relative risks (RRs), with 95% confidence intervals. When clinically interpretable, the number needed to treat, or harm, will be calculated from absolute risk differences. Effect sizes for differences in proportions will be estimated using Cohen’s *h*.

Model diagnostics will be examined to assess distributional assumptions, heteroscedasticity, and influential observations. If substantial departures are detected, robust linear mixed-effects models preserving the same fixed- and random-effects structure as the primary models will be considered. Sensitivity analyses may include restricted longitudinal data analysis under a common-baseline assumption of baseline variables showing clinically relevant imbalance between groups (70). Effect modification by sex, pubertal status, insulin delivery modality, insulin type, and CGM system will be explored by adding interaction terms to the primary model. These analyses will be considered exploratory.

Other exploratory analyses: Exploratory analyses will examine whether the magnitude of the intervention effect varies according to intervention exposure, adherence, and training-related characteristics. Dose–response analyses will use app-derived indicators of intervention exposure, including training frequency, completion of prescribed sessions, accumulated training volume, session duration, active and recovery times, training time, training type, and, when available, heart-rate metrics or perceived exertion. We will also explore whether within-participant changes in the primary and secondary outcomes are associated with changes in other clinical, behavioral, and physical-fitness variables. These change–change associations will be examined using regression models adjusted for treatment group, baseline values, hospital, and other relevant prespecified covariates. All such analyses will be considered exploratory and will not be interpreted as providing evidence of causal relationships.

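### The covariate-free primary handgrip model leaves out pubertal maturity, which is recorded before randomisation, and so gives up a modest amount of precision

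*Protocol article*

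**What the plan says.** All references are to the protocol article.

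- **Population and outcome.** Section 2.3 enrols ages 10 to 18. Section 2.9 defines the primary outcome as the change from baseline to 12 weeks in a handgrip z-score standardised by age and sex.
- **Maturity data.** Section 2.10.5 defines two measures: "Pubertal status will be assessed using Tanner criteria", rated by a physician, and estimated distance from peak height velocity (PHV), grouped as prepubertal, peri-pubertal or post-pubertal. Section 2.11 places collection of pubertal-maturation data at the baseline clinical visit, before central randomisation.
- **Allocation.** Section 2.5: "The algorithm will use a non-stratified randomization scheme with small, randomly varying even block sizes".
- **Primary model.** Section 2.15 fits group, time and group × time, with random intercepts for hospital and for participant within hospital. It then states: "The primary model for handgrip strength will include no additional covariates". The glycemic and insulin models do receive covariates, chosen for their prognostic value. Any unplanned adjusted analysis is to be labelled post hoc.
- **Other use of maturity.** Only exploratory: "Effect modification by sex, pubertal status, insulin delivery modality, insulin type, and CGM system will be explored".

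**The concern.** The trial spans puberty. Standardising for chronological age and sex removes the average growth in strength for a child of that age and sex. It does not remove the departure of an early or late maturer from age peers. A participant in the growth spurt may gain z-score over the follow-up, while one of the same age and sex who is before or past it may not. The participant random intercept absorbs stable differences in level but not differences in change, and the treatment effect is a difference in change.

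The variance that baseline maturity could explain therefore stays in the residual. The plan accepts prognostic value as grounds for covariates in its glycemic and insulin models, but gives no reason for having none in the primary model. Because that choice is fixed, a maturity-adjusted handgrip estimate produced later would count as post hoc. What is at stake is the width of the confidence interval for the primary contrast, and some power.

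**Working it through.** **1. Inputs from section 2.4**

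- Raw effect: "the between-group difference in handgrip strength z-score was 0.24 units".
- Standardised effect: d = 0.56.
- Test: "Using G*Power for an independent-samples comparison with a two-sided" α of 0.05.
- Result: "134 evaluable participants (67 per group) would provide 89.6% power, rounded to approximately 90"%.

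**2. Reproducing the plan's figure**

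Noncentral-t power for two independent means, with d = 0.56 and n = 67 per arm, is 89.57%. This agrees with the stated 89.6%.

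Implied SD = 0.24 / 0.56 = 0.43 z. I take this as the SD of change, which the protocol does not say in so many words.

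Standard error of the contrast = 0.43 × √(2/67) = 0.074 z.

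**3. Variance that maturity might explain**

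The documents give no figure, so two assumptions are needed: a share p = 40% of participants who are peri-pubertal, and a difference δ of 0.1 to 0.3 z in 12-week change between them and the rest.

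R² = p(1 − p)δ² / SD² = 0.24 × δ² / 0.1837

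**4. Power after adjustment**

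The same power function is used with d / √(1 − R²) and 67 per arm. The standard error is multiplied by √(1 − R²).

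| δ (assumed) | R² | adjusted d | power | standard error |
|---|---|---|---|---|
| none | 0 | 0.560 | 89.6% | 0.074 |
| 0.1 | 1.3% | 0.564 | 90.0% | 0.074 |
| 0.2 | 5.2% | 0.575 | 91.1% | 0.072 |
| 0.3 | 11.8% | 0.596 | 92.9% | 0.070 |

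At R² = 5%, 64 per arm with adjustment would match the present power. At R² = 10%, 61 per arm would.

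**5. Why the interaction with time is needed**

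The treatment effect is the group × time coefficient, a between-group difference in change. A maturity main effect shifts a participant's baseline and 12-week values equally, so it leaves that contrast essentially unadjusted. Only maturity × time can absorb maturity-related change.

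**6. Size of a chance imbalance, for scale**

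With p = 40% and 67 per arm, the between-arm difference in peri-pubertal share has SD √(2 × 0.4 × 0.6 / 67) = 8.5 percentage points. A 1-in-20 gap is 1.96 × 8.5 = 16.6 points. Multiplied by δ of 0.1 to 0.3, it moves the estimate by 0.017 to 0.050 z, which is about 0.2 to 0.7 standard errors. The unadjusted standard error already allows for movements of this kind.

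**The case against.** The strongest reply is that nothing here is an error. Blocked central randomisation with a fully prespecified unadjusted model is valid, and adding a prognostic term is a question of efficiency. Age and sex standardisation together with the within-participant contrast already remove much of the maturity signal. The upper assumed difference, 0.3 z, exceeds the 0.24 z effect on which the trial is sized, so the true gain may lie near the low end, at under half a point of power. Pubertal status is also to be explored as an effect modifier.

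Most of this stands, and it limits the point to a modest improvement. It does not remove it. The standardisation and the random intercept leave maturity-related departures in change untouched. The exploratory interactions ask whether the effect differs by stage and do not supply a maturity-adjusted primary estimate.

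A reader might infer three stronger things that the documents do not support:

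- **That randomisation should have been stratified by maturity.** It need not be. Adjustment in the model recovers the precision with allocation as planned.
- **That a chance imbalance in maturity would bias the result or go uncovered.** Randomisation keeps the estimate unbiased, and chance imbalance is already reflected in the standard error and the type I error rate.
- **That the planned power is overstated.** The calculation is unadjusted and reproduces. If the earlier trial's SD was also unadjusted, maturity-related variation is already inside it.

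**Conclusion.** The point holds as a low-severity loss of precision in the primary analysis. Under the assumed 1% to 12% of variance in change explained by maturity, adjustment would raise power at 67 per arm from 89.6% to about 90% to 93% and reduce the standard error from 0.074 z to between about 0.074 and 0.070 z. These figures rest on the assumed peri-pubertal share, on the assumed difference in change, and on reading 0.43 z as the SD of change. The documents do not fix the true gain, and it could be smaller. The estimate is unbiased with or without the change, and no figure in the sample-size section needs correcting.

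**What to change.** In section 2.15, replace the statement that the handgrip model has no additional covariates with one prespecified baseline maturity measure, entered as a main effect plus its interaction with time. Name a single measure and its coding in advance so that no analyst choice is introduced. A categorical form is preferable, for example the pre-, peri- and post-PHV groups of section 2.10.5. A linear term in years from PHV would poorly capture a gain that peaks around PHV. State which group takes values exactly at −1 and +1 year, since the published limits overlap there. Report the model without the maturity terms as a sensitivity analysis, and leave the randomisation as it is.

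If the investigators prefer to keep the unadjusted model as primary, naming the maturity × time model as a prespecified sensitivity analysis would at least spare it post hoc status.

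The cost is a sentence or two before unblinding and about two to four degrees of freedom. With three groups that is two for the main effect and two for the interaction. No new data are needed.

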#### Insulin requirements

2.10.2

During pre-project meetings, clinical teams noted that young people not using AID pumps do not routinely enter insulin data into their CGM systems. Therefore, at the baseline and 12-week visits, these participants will be instructed to prospectively record carbohydrate intake and insulin doses for the following 7 days. Daily carbohydrate intake and insulin doses, including basal insulin, rapid-acting boluses, correction boluses, and total daily insulin, will be collected and averaged over this 7-day period.

For participants using AID pumps, carbohydrate intake and insulin-dose data will be extracted from the corresponding pump software, regardless of device brand. Data will be obtained for the 7 days following each visit to ensure comparability with participants not using AID pumps. In addition, 14-day pre-visit data will be extracted for AID pump users and used in future within-group subanalyses.

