### Participant timeline

2.11

Each participant will follow a standardized timeline comprising screening and enrolment, baseline assessment, randomization, a 12-week intervention or usual-care period, post-intervention assessment, and post-T1 data collection. Screening and informed consent or assent may be initiated before the baseline visit.

Baseline procedures will be completed in the following sequence: (i) a baseline clinical visit, during which eligibility will be confirmed, informed consent or written assent will be verified, and sociodemographic, diabetes-related clinical, anthropometric, pubertal-maturation, and handgrip-strength data will be collected; (ii) central randomization immediately after the baseline clinical data have been entered into the Diactive-1 web platform; (iii) completion of the online web-based questionnaires within 48 hours after the baseline visit; (iv) a 7-day baseline data-collection period, during which participants will undergo fasting blood and urine testing and upload all available glucose-monitoring, insulin, and carbohydrate-intake data from their CGM system or insulin pump; (v) upload of the laboratory results and CGM or insulin-pump reports by the clinical research team within the following 72 hours, including glucose-monitoring data covering the 14 days before and 7 days after the baseline clinical visit; and (vi) verification of the completeness of all baseline information, followed by activation of the Diactive-1 app for participants allocated to the intervention group. Thus, intervention exposure will begin only after all baseline assessments and data-collection procedures have been completed and verified. The 12-week intervention or usual-care follow-up period will begin on the date of app activation or the corresponding date for participants allocated to usual care. To facilitate scheduling of the final clinical assessment, the web platform will generate automated alerts 15 and 7 days before the expected Week 12 assessment.

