**Figure 4 f4:**
[figure not shown]
Overview of the Diactive-1 study timeline, including baseline procedures, randomization, intervention and usual-care periods, and post-intervention assessments.

**Table 2 T2:** Schedule depicting the enrollment and interventions for the Diactive-1 Study in accordance with the SPIRIT 2025 guidelines.

Randomization	TRIAL PERIOD			
	Enrollment		Pre-randomization	Post-randomization
Timepoint	*-t_i_* to 0	0	*Baseline t_0_*	*t_1 (12 weeks)_*
ENROLLMENT:				
Eligibility screen	X	X*		
Informed consent	X	X*		
Randomization		X		
INTERVENTION/COMPARATOR:				
Diactive-1 ^a^			↔	↔
Usual care ^b^			↔	↔
ASSESSMENTS:				
Handgrip strength			X	X
Glycemic stability			X	X
Insulin requirements			X	X
Cardiovascular biomarkers and lipid profile			X	X
Anthropometric parameters			X	X
Maturity status			X	X
Self-reported fitness			X	X
Physical literacy			X	X
24-Hour Movement Patterns			X	X
Barriers to physical activity			X	X
Sociodemographic information			X	
Psychological assessments			X	X
Quality of life for youth			X	X
Quality of life for families			X	X
Mediterranean diet			X	X
Eating disorders			X	X
App usability (users/experts)^c^				X
Diactive-1 app parameters^d^			↔	↔

Note: X indicates an assessment or procedure performed at the corresponding timepoint; ↔ indicates continuous delivery, usual-care exposure, or app-based data recording throughout the 12-week study period. Baseline clinical assessments will be completed before randomization, whereas the remaining baseline questionnaires and 7-day diabetes-related data collection will be completed after randomization but before intervention activation.

*Eligibility and consent may be screened before enrolment and confirmed at the baseline visit before randomization.

^a^
Diactive-1 will be activated only after all baseline procedures and data have been completed and verified and will then be delivered for 12 weeks.

^b^
Participants allocated to the usual-care/waiting-list control group will receive usual clinical care during the 12-week study period and will be offered Diactive-1 access after post-T1 7-day data collection.

^c^
App usability will be assessed at the end of the intervention period among participants with access to the app; expert MARS assessment will be reported separately if not linked to participant follow-up.

^d^
Diactive-1 app parameters will be recorded continuously during app use and summarized at the end of the intervention period.

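### Randomisation precedes the baseline questionnaires, the 7-day insulin and carbohydrate record and the laboratory tests, so some non-primary baselines may be recorded by people who know their arm

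*Protocol article*

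**What the plan says.** Section 2.5 has the platform randomise automatically after the baseline clinical visit and "entry of the corresponding clinical data, before the 7-day diabetes-related data-collection period".

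The participant timeline (section 2.11) gives six baseline steps. Step (i) is the clinical visit, with handgrip, anthropometry, pubertal stage and clinical data. Step (ii) is "central randomization immediately after the baseline clinical data have been entered into the Diactive-1 web platform". Step (iii) is "completion of the online web-based questionnaires within 48 hours after the baseline visit". Step (iv) is "a 7-day baseline data-collection period, during which participants will undergo fasting blood and urine testing", together with upload of glucose, insulin and carbohydrate data. Step (v) is upload of laboratory results and device reports by the clinical team within a further 72 hours. Step (vi) is verification that baseline is complete, followed by app activation in the intervention arm.

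The note under Table 2 confirms the order: "the remaining baseline questionnaires and 7-day diabetes-related data collection will be completed after randomization but before intervention activation". Section 2.10.2 has participants without an automated insulin delivery (AID) pump "instructed to prospectively record carbohydrate intake and insulin doses for the following 7 days", and takes the same post-visit week from the pump software for AID users.

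On blinding, section 2.5 says: "Participants and healthcare professionals cannot be blinded due to the nature of the intervention". Section 2.6 has the platform call the randomisation module once baseline data are entered and verified, and then produce instructions specific to each group.

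Section 2.15 models baseline and week 12 as repeated outcomes and takes the group × time interaction as the effect. It adds baseline insulin dose and baseline carbohydrate intake as covariates for the glycaemic outcomes, and baseline carbohydrate intake for insulin dose.

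**The concern.** A baseline is protected by randomisation only if it is taken before allocation, or at least before anyone supplying the data knows the allocation. Here several baselines come afterwards, in a wait-list trial without blinding. A participant told to wait may answer a well-being questionnaire differently, one told to train may report more motivation, and insulin dosing or its recording may change in anticipation. People may also complete the baseline selectively by arm. Any such difference enters the change score and so the treatment effect. An analysis that assumes a common baseline does not repair it, because randomisation does not guarantee equal baselines for values recorded after it.

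The document also disagrees with itself. Table 2 puts all these assessments in a column headed as pre-randomisation, while its own note says they come after. Section 2.6 puts randomisation after verification of baseline data, while section 2.11 puts the completeness check at step (vi), four steps after randomisation.

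**Working it through.** **1. Which baselines precede randomisation (sections 2.10.1, 2.10.2, 2.11, Table 2)**

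| Measurement | When taken | Status |
|---|---|---|
| Handgrip (primary) | Step (i) | Before randomisation; not affected |
| CGM outcomes (key secondary) | 14 days before the visit | Before randomisation; not affected as outcomes |
| Insulin requirements (key secondary) and carbohydrate, non-AID users | Self-recorded over 7 days after the visit | After; higher risk |
| The same, AID users | Pump download, same 7 days | After; lower risk |
| Questionnaires with a baseline | Within 48 hours after the visit | After; higher risk |
| Laboratory values | Within the 7-day period | After; lower risk |
| User app rating (uMARS) | Week 12 only | No baseline; not concerned |

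**2. Whether the arm is known by then.** Randomisation is at step (ii), there is no blinding, and section 2.6 ties group-specific instructions to the randomisation call. The questionnaires are online and come after that call. No section delays release of the allocation to step (vi). Early knowledge is therefore a reasonable inference, not a stated fact.

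**3. How a baseline shift reaches the estimate.** With I and C for the intervention and control means, and 0 and 1 for baseline and week 12, the interaction estimates (I1 − I0) − (C1 − C0). Let τ be the true effect. If knowing the allocation moves the between-arm baseline difference by δ and leaves week 12 alone, the expected estimate is τ − δ. If a fraction λ of the shift persists to week 12, it is τ − δ + λδ.

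Signs: lower control well-being at baseline or higher intervention motivation at baseline gives δ > 0 on a scale where high is good, so the benefit shrinks. An anticipatory insulin reduction in the intervention arm lowers its baseline, so the later reduction looks smaller.

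**4. The plan's own figures.** Section 2.4 states 89.6% power for 67 per group at d = 0.56, two-sided α = 0.05. A noncentral t calculation gives 89.57%, and 134/(1 − 0.15) = 157.6, rounded up to 158. Both reproduce. They concern handgrip and do not change.

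**5. Illustration.** Assumptions not in the protocol for the affected outcomes: 67 per arm, baseline to week-12 correlation ρ of 0.5 or 0.7, δ of 0.1 or 0.2 SD, λ = 0, τ = 0, and a single two-sided 5% test without multiplicity correction.

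SE = √(2(1 − ρ)) × √(2/67), in SD units. For ρ = 0.5: 1.000 × 0.173 = 0.173. For ρ = 0.7: 0.775 × 0.173 = 0.134.

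Rejection probability = [1 − Φ(1.96 − δ/SE)] + Φ(−1.96 − δ/SE). The first term is rejection in the direction of the bias.

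| ρ | δ | δ/SE | In direction of bias | Opposite | Total |
|---|---|---|---|---|---|
| 0.5 | 0 | 0 | 2.5% | 2.5% | 5% |
| 0.5 | 0.1 | 0.579 | 8.4% | 0.6% | 9% |
| 0.5 | 0.2 | 1.158 | 21.1% | 0.1% | 21% |
| 0.7 | 0.1 | 0.747 | 11.3% | 0.3% | 12% |
| 0.7 | 0.2 | 1.494 | 32.1% | 0.03% | 32% |

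Under the mechanisms in step 3, the direction of bias is against the intervention.

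**The case against.** The case for leaving this alone has real weight, and most of it limits the point without removing it.

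- **Importance.** The primary outcome and one of the two key secondary families have clean baselines. Apart from insulin requirements, section 2.10 classes the affected outcomes as exploratory, or as contextual in the case of barriers to activity. This stands and sets the priority at moderate.
- **False positives.** A reader might infer from the rejection rates that the design will produce spurious benefits. It does not follow. The shifts and correlations are assumed, secondary outcomes carry a Benjamini–Hochberg correction, and for the mechanisms one would expect, nearly all the excess is rejection against the intervention.
- **Persistence.** If the same reporting tendency lasts to week 12, subtraction cancels part of it (λ above 0), whereas a clean baseline would leave the week-12 reporting bias in place. That is correct. But λ is unknown, will differ between instruments and cannot be checked from the data, so cancellation is not something to plan on.
- **Disclosure.** A reader might take it as stated that families know their arm when they fill in the baseline. The protocol gives no time of disclosure, and the wording of section 2.6 could be read as later release. The point rests on the absence of any step that withholds allocation.
- **Scope.** A reader might extend this to every self-reported and laboratory measure. The uMARS has no baseline, laboratory samples are processed by technicians outside the project, AID insulin data are downloads, and the locked app means treatment itself cannot contaminate baseline.
- **Table 2.** Its note already tells the truth about the order. The column heading still contradicts the note.

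**Conclusion.** The sequence is explicit in sections 2.5 and 2.11 and in the Table 2 note, and it is a moderate weakness confined to non-primary outcomes. It concerns the baseline of insulin requirements, mainly as self-recorded by non-AID users; the questionnaires that have a baseline; and the two covariates. For the covariates the consequence is probably smaller: one entered only as a main effect moves both time points alike.

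A baseline-only shift passes one-for-one, with opposite sign, into the group × time estimate. Whether such a shift occurs, and its size, cannot be known from the protocol. The 9% to 32% range is an illustration under the assumptions listed, not an estimate for this trial. The more likely harm is a hidden benefit on insulin requirements or well-being. The limitations in the Discussion name lack of blinding and self-report but not this ordering. The conclusion on disclosure would change if the full protocol or platform specification withholds allocation until step (vi); the table heading and section 2.6 would still need reconciling.

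**What to change.** Move the randomisation trigger from step (ii) to step (vi): after baseline completeness is verified and immediately before app activation, identically in both arms. If the trigger cannot move, withhold release of the allocation to families and sites until step (vi). Start the 12-week clock on that date in both arms, which also defines the control arm's start date. Align sections 2.5, 2.6 and 2.11 and the Table 2 heading.

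If anyone has already been randomised under the present order, flag them, state the limitation, and add a sensitivity analysis for the affected outcomes that uses no post-randomisation baseline, namely a week-12 comparison between arms. For AID users, the 14-day pre-visit pump data that section 2.10.2 already extracts could supply a clean insulin baseline.

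**Cost.** A workflow change and a short amendment, with no extra visit and no later start, because the app is locked until step (vi) anyway. Allocation reaches families about 10 days after the visit (7 days plus 72 hours). If enrolment has begun there will be two baseline regimes. The week-12 comparison has SE √(2/67) = 0.173 SD: equal to the change contrast at ρ = 0.5, and 0.173/0.134 = 1.29 times as large at ρ = 0.7. It also leaves any reporting bias at week 12 untouched.
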